### Assignment of interventions

The trial is open-labeled but a central random blind-generated allocation was performed before the first home visit. The methodological referent of PREVED study enrolled the participants. A number was assigned to each participant. The random blind-generated allocation with 1:1:1 ratio is based on fixed blocks of 3 before the first home visit. The allocation sequence is generated on Microsoft EXCEL® (function RAND) by a doctoral student. Participants were then randomly assigned to one of the three groups by a research nurse who is also trained in indoor environments.

This type of study design did not allow a blinded trial as is the case in intervention research.

No changes were planned to randomly assigned groups.

### Data collection, management, and analysis

The research nurse performs home visits and collected data at four key moments (Table 5):
Home visit 1: Q1, Q2, and urine analysisHome visit 2: Q1, Q2, and urine analysisChildbirth: childbirth data, urine, and colostrum analysisHome visit 3: Q1 and Q2

Data input is entered by the research nurse and by the study site coordinator on electronic case report forms (e-CRF). Quality control and queries are carried out regularly. Telephone reminders are expected, if necessary, for home visits 2 and 3.

Urine and colostrum samples are collected in glassware provided by the investigator. They are stored at − 80 °C, in polypropylene tubes, in the Biological Resource Centre of the University Hospital of Poitiers (no. BB-0033-00068) for 5 years. These samples are analyzed using reliable ultrasensitive methods previously developed by our research team for BPA and its chlorinated derivatives [54, 55] and new methods for PB developed for this study. All laboratory materials and solvents are tested to ensure that they were free of contamination from target compounds. High-quality compounds and solvents are supplied by reagent manufacturers. Samples are prepared and extracted. Analyte concentrations are determined using Ultra Performance Liquid Chromatography (Shimadzu®, Kyoto, Japan) coupled to an API 6500+ mass spectrometer (ABSciex®, Concord, Canada) equipped with an electrospray ionization (ESI) interface, operating in negative ionization mode. Target analytes are analyzed in multiple-reaction monitoring (MRM) mode using two specific transitions per analyte to ensure the selectivity and the sensitivity of the method. The analytical methods used are validated according to international guidelines [56–59]. These methods allow to detect and quantify trace concentrations of unconjugated forms of BPA, its chlorinated derivatives, and PB. Urinary concentrations of analytes are corrected using urinary creatinine concentrations determined with a Cobas® 8000 (Roche Diagnostics, Mannheim, Germany) and using urinary specific gravity determined with a hand-held refractometer.

Firstly, a descriptive analysis will be performed on sociodemographic data, questionnaire scores, and on EDC concentrations with percentage for qualitative variables and mean, standard deviation, median, maximum, and minimum for quantitative variables.

Baseline measurements of the three trial arms will be compared using paired *t* tests and *χ*^2^ tests for the analysis of Q1 and EDC concentrations. The results of Q2 in the three groups will be compared by dimension using ANOVA analyses. An intention-to-treat analysis will carried out, and then a per-protocol analysis in aim to take into account population relating to protocol non-adherence.

Main outcome will be compared between home visit 1 and home visit 2. The rest of analysis will be performed between home visit 1, home visit 2, and home visit 3. Multivariate logistic regression will be performed to assess factors influencing main and secondary outcomes.

All statistical analyses will be performed using SAS 9.4® (SAS Institute, Cary, North Carolina, USA).

No interim analyses are scheduled.

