## Methods

### Study design

The PREVED study is an ongoing open-label, monocentric, randomized (1:1:1) controlled superiority trial, parallel-designed, three-armed with:
A control group: group (1)An intervention group in neutral location: group (2)An intervention group in contextualized location: group (3)

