### Sample size

According to the results of the EDDS (Endocrine Disruptors Deux-Sèvres) cohort study, 83% of French women consumed canned food [48]. Thus, we calculated the number of participants based on the primary outcome measure (consumption measure) using a two-sided paired sample *t* test with 0.05 level of significance two-way design and *β* = 0.20. Our hypothesis was that the contextualized intervention would decrease this percentage to 60%, representing a decrease of 23 points, and 58 participants were required for each group. We expected 20% of lost to follow-up participants; consequently, 70 participants are required for each group, out of a total of 210 pregnant women to be included in our study. This number was increased to 273 persons due to significant colostrum loss in an amendment submitted to the Committee for Personal Protection who approved the first protocol (protocol version 10 approved by the Committee for Personal Protection on 15 June 2018).

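### Paired t tests are assigned to the baseline comparison of three independent, unmatched arms; for EDC concentrations and continuous Q1 items the test cannot be run as written

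*Protocol article*

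**What the plan says.** The section on data collection, management and analysis in the protocol article says: "Baseline measurements of the three trial arms will be compared using paired" t tests and chi-square "tests for the analysis of Q1 and EDC concentrations". The next sentence uses a between-group method for the psychosocial questionnaire: "The results of Q2 in the three groups will be compared by dimension using ANOVA analyses".

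The study design section describes a "randomized (1:1:1) controlled superiority trial, parallel-designed, three-armed" trial. The section on assignment of interventions adds: "The random blind-generated allocation with 1:1:1 ratio is based on fixed blocks of 3 before the first home visit". It describes no matching of women. The visit list and Table 5 give one Q1, one Q2 and one urine measurement per woman at home visit 1.

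The analysis section also plans descriptive statistics for sociodemographic data, questionnaire scores and EDC concentrations: percentages for qualitative variables; mean, standard deviation, median, minimum and maximum for quantitative ones.

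**The concern.** A paired t test works on differences within defined pairs: two values from one person, or values from two people matched by design. At baseline each woman contributes one value and belongs to one arm, so nothing defines which woman in one arm goes with which woman in another. The test also takes two columns, and there are three arms.

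If an analyst ran it anyway, software would pair women by their order in the file. The p value would change when the file is re-sorted, and women without a partner would be lost when arm sizes differ. What is at stake is the baseline table for EDC concentrations and continuous Q1 items, and any use later made of its p values.

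**Working it through.** **Step 1. Is there a pairing?** Setting the sections side by side:

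- Study design: parallel, three arms.
- Assignment of interventions: individual allocation in blocks of 3. A block balances the numbers over time; the article does not present its three women as a matched set.
- Table 5 and the visit list: one baseline value per woman.
- Analysis: paired t test between arms.

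No section defines a pair between arms, and none corrects the sentence.

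**Step 2. Which variables are affected?** Only those to which a t test would apply: EDC concentrations and any continuous Q1 item. Chi-square tests suit categorical Q1 items, and ANOVA suits Q2 across three groups.

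**Step 3. How far does an arbitrary pairing move the p value?** The baseline sentence carries no figure of its own to reproduce. Inputs: 273 women in total (sample size section), and equal arms as an assumption, so 273/3 = 91 per arm; approximately normal data with equal SDs.

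- With equal SDs, paired t = unpaired t / √(1 − r), where r is the sample correlation that the arbitrary pairing happens to produce.
- Over random pairings, r has mean 0 and SD about 1/√90 = 0.105, so 95% lie within ±1.96 × 0.105 = ±0.207.
- An unpaired p of 0.05 on 180 degrees of freedom is t = 1.973.
- r = −0.207: t = 1.973/√1.207 = 1.80, p = 0.076 on 90 degrees of freedom.
- r = +0.207: t = 1.973/√0.793 = 2.22, p = 0.029.

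A simulation of 20,000 random pairings of one such data set gave a 95% range of 0.029 to 0.076, in agreement. A separate simulated data set with 70 per arm and an unpaired p of 0.118 gave paired p values from 0.046 to 0.190 over 5,000 re-pairings (full range).

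This is the case closest to the threshold. Starting from an unpaired p of 0.50 (t = 0.676), the same formula gives about 0.45 to 0.54.

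**Step 4. Is the error rate inflated?** No. With 70 per arm, 40,000 null data sets, normal data and equal arms, the arbitrarily paired test rejected in 5.1% and the independent test in 5.0%. Degrees of freedom fall from 138 to 69, which moves the critical value only from 1.977 to 1.995.

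**Step 5. Does the sample size depend on this sentence?** No. The sample size section assumes that "83% of French women consumed canned food" and that "the contextualized intervention would decrease this percentage to 60"%, and states 58 per group. Formulas for two independent proportions (two-sided 0.05, power 80%) give 57 (unpooled variance), 58.2 (arcsine) and 60 (pooled variance). These bracket the stated 58, and the baseline test enters none of them.

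**The case against.** The sentence may be a compressed mixture: chi-square tests between arms, and paired t tests for change within a woman between visits. The sample size section also names a paired t test, and the paragraph that follows compares visits without naming a simple test. This reading is possible, but the sentence speaks of baseline measurements of the three arms, which does not fit it. The sentence needs rewriting on either reading. What stands of the objection is that deleting it outright would be risky, because it is the only place that names simple tests for Q1 and EDC concentrations.

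Three stronger readings are tempting, and the documents do not support them.

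- *The whole baseline analysis is invalid and its p values meaningless.* The chi-square tests and the ANOVA are suitable for their variables, and the error rate under arbitrary pairing stays near 5%. The fault is an undefined pairing.
- *There is a 60% chance of a false baseline difference.* This comes from 1 − 0.95^18 = 0.603, for six analytes (an assumed count: BPA, at least one chlorinated derivative and four parabens) and three arm pairs. The pairs share arms, so the 18 tests are not independent. Simulation gives about 12% per analyte, hence 1 − 0.88^6 = about 54% if the analytes are independent; correlation between them would normally lower it. A correct unpaired test has the same multiplicity, so neither figure measures this error.
- *Arbitrary p values will steer the adjusted results.* The discussion plans adjustment for confounders of the psychosocial dimensions highlighted in the study, but no section links that choice to baseline tests. It is worth ruling out explicitly, but it is not something the plan states.

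**Conclusion.** The point holds as a wrongly stated analysis, limited to EDC concentrations and any continuous Q1 items at baseline. It is not a detail left to a fuller document: the article names a test that its own design does not permit. The size is modest. In the borderline case, re-sorting the file moves p between about 0.03 and 0.08; away from the threshold the conclusion rarely changes. These figures assume equal arms of 91, near-normal data and equal SDs. With unequal arms some women would also be discarded. As worded, the sentence touches neither the sample size nor the primary comparison of home visits 1 and 2, so the impact is minor.

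**What to change.** Rewrite the sentence so that it does three things.

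1. Report home visit 1 values by arm, using the descriptive statistics already planned, without p values: chance differences are expected between randomised arms, and a test of them answers little. If tests are kept, use a method for independent groups, such as one-way ANOVA (on log concentrations for EDCs) or Kruskal-Wallis.
2. Reserve paired tests for change within a woman between visits, and say so.
3. State that baseline p values will not be used to choose adjustment covariates.

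The cost is negligible: one sentence is reworded and no sample-size figure changes. The data availability statement says that the data had yet to be analysed, so on that footing the correction can precede the analysis.

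### The plan names ANOVA for the Q2 psychosocial scores and does not say how each woman's own home visit 1 score is used; analysis of covariance on that score would be at least as precise at almost no cost

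*Protocol article*

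**What the plan says.** All references are to the protocol article.

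- **Outcome.** The Secondary outcomes section lists the mean Q2 score first. Its dimensions are in Table 4. Several are scores or visual analogue scales; others, such as the trusted person, are not quantitative.
- **Timing.** Table 5 and the visit list under Data collection, management, and analysis place Q2 at home visits 1, 2 and 3 (t0, t+2 months, t+14 months). The workshops are at t+1 month, so home visit 1 gives a pre-workshop score for each woman.
- **Test.** The same section states: "The results of Q2 in the three groups will be compared by dimension using ANOVA analyses". This sentence comes directly after the one on comparing baseline measurements across arms.
- **Visits.** The next paragraph sets the main outcome between home visits 1 and 2 and then says: "The rest of analysis will be performed between home visit 1, home visit 2, and home visit 3".
- **Other modelling.** Logistic regression is planned for factors that influence the main and secondary outcomes. The Discussion promises adjustment for confounders of the psychosocial dimensions. Neither statement mentions the woman's own earlier Q2 score.
- **Sample size.** The calculation concerns the consumption outcome only: "would decrease this percentage to 60%, representing a decrease of 23 points, and 58 participants were required for each group". For attrition: "We expected 20% of lost to follow-up participants". For the later total: "This number was increased to 273 persons due to significant colostrum loss". No effect, standard deviation, correlation or power is given for Q2.

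**The concern.** ANOVA is the only between-arm comparison named for Q2 scores. The article names a test but no baseline covariate, change score, repeated-measures term or arm-by-visit contrast, although a baseline score exists by design for each woman. An attitude or knowledge score will usually correlate with the same woman's earlier score, and adjusting for it removes that share of the variance from the arm comparison.

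At stake is precision on the first-listed secondary outcome, which the Discussion presents as something earlier studies did not provide. The trial was not sized on Q2, so any avoidable loss of precision falls directly on these comparisons.

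**Working it through.** **1. Inputs from the article.** Three arms, 1:1:1. Two-sided alpha 0.05 (stated for the main outcome). Planned evaluable women per arm: 58. After the increase: 273/3 = 91, less 20% = 72.8, about 73.

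**2. The plan's own figure.** The 58 per group belongs to the main outcome (83% against 60%, alpha 0.05, power 0.80). An independent two-proportion calculation gives 58.2 by the arcsine formula and 60 by the pooled formula, so 58 is reproduced closely enough. It is used below only as an arm size. There is no Q2 figure to reproduce.

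**3. Assumptions, because the article gives none for Q2.** Standardised arm means of 0, 0.4 and 0.4 SD. Correlation rho between the home visit 1 and follow-up scores of 0.3, 0.5 and 0.7.

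**4. ANOVA of a follow-up score against ANCOVA.** The grand mean is 0.8/3 = 0.267. The squared deviations sum to 0.0711 + 0.0178 + 0.0178 = 0.1067. ANOVA noncentrality is n × 0.1067, with 2 and 3n − 3 degrees of freedom. For ANCOVA it is divided by (1 − rho²), with one denominator degree of freedom fewer.

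| n per arm | Analysis | Noncentrality | Omnibus power |
|---|---|---|---|
| 72.8 | ANOVA of follow-up | 7.77 | 69.7% |
| 72.8 | ANCOVA, rho 0.3 | 7.77/0.91 = 8.53 | 74.1% |
| 72.8 | ANCOVA, rho 0.5 | 7.77/0.75 = 10.35 | 82.4% |
| 72.8 | ANCOVA, rho 0.7 | 7.77/0.51 = 15.23 | 94.4% |
| 58 | ANOVA of follow-up | 6.19 | 59.0% |
| 58 | ANCOVA, rho 0.3 | 6.80 | 63.4% |
| 58 | ANCOVA, rho 0.5 | 8.25 | 72.4% |
| 58 | ANCOVA, rho 0.7 | 12.13 | 88.1% |

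At rho 0.5 the covariate is worth 1/0.75 = 1.33, that is, a third more women. At rho 0 nothing is gained.

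**5. A check that does not depend on the 0.4 SD.** Take the pairwise effect at which ANOVA of follow-up has 80% power. ANCOVA then has 83.6%, 89.9% and 97.5% at rho 0.3, 0.5 and 0.7.

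**6. The other readings.**

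- *Change scores.* The variance factor is 2(1 − rho), against (1 − rho)(1 + rho) for ANCOVA. Since 1 + rho cannot exceed 2, ANCOVA is never less precise, apart from its one degree of freedom. From the same 80% base, change-score power is 65.8%, 80.0% and 95.1%, so it beats follow-up-only ANOVA only above rho 0.5.
- *Repeated-measures ANOVA with home visit 1 as a response.* This respects the pairing, but the arm main effect averages in a visit at which the workshops cannot yet have acted. A 0.4 SD shift at both follow-ups becomes (0 + 0.4 + 0.4)/3 = 0.267 SD. With equal correlations between visits, the variance of a woman's mean is (1 + 2 rho)/3. The noncentrality is therefore multiplied by (4/9)/((1 + 2 rho)/3) = 0.83, 0.67 and 0.56 relative to one follow-up visit alone. The informative term is arm-by-visit, which is not named.
- *Baseline comparison only.* Then the article names no post-workshop comparison of Q2 scores between arms.

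**The case against.** The strongest reply is that the article never says the baseline score is left out. The term ANOVA covers repeated-measures and change-score analyses, and the sentence on performing the remaining analyses across the three home visits fits either. The sentence may even be the second half of the baseline comparison that it follows. The full protocol or SAP, which is not shown, may give the model. An unadjusted ANOVA of follow-up scores is unbiased under randomisation, the outcome is secondary, and the gain depends on a correlation that the article does not give; at 0.3 it is only about 4 points of power.

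Most of this stands. A reader might infer that the plan ignores the home visit 1 score; the text supports only that no use of it is stated. A reader might also infer that all three visits are to be pooled as independent observations in one ordinary ANOVA. That would raise the false-positive rate for arm from 5% to roughly 0.05^(1/(1 + 2 rho)), about 15%, 22% and 29% at rho 0.3, 0.5 and 0.7. But nothing in the article says that scores are stacked, and a comparison between visits is not a pooling of them. The figure is a caution for whoever programs the analysis, not a description of the plan.

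What the reply does not remove is that the article chose to name a test, and none of the plausible readings of it improves on adjustment for the home visit 1 score. The promised adjustment for confounders does not name that score, and logistic regression does not directly model a mean score.

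**Conclusion.** The point holds as a free improvement to the wording, not as an error that invalidates the Q2 analysis. On the follow-up reading the comparison is valid and loses only precision: about 4, 13 and 25 points of omnibus power at rho 0.3, 0.5 and 0.7 with about 73 women per arm (70% against 74%, 82% and 94%). At 58 per arm the contrast is 59% against 63%, 72% and 88%. These sizes rest on the assumed 0.4 SD shift in both workshop arms and the assumed correlations. What needs no assumed effect is the direction: apart from one degree of freedom, ANCOVA is at least as precise as ANOVA of follow-up or of change.

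The sponsor should make the change, with medium confidence, since the full protocol or SAP may already contain it.

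**What to change.** Replace the Q2 sentence with wording such as:

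> For each quantitative Q2 score, the home visit 2 score, and separately the home visit 3 score, will be compared between the three randomised groups by analysis of covariance with the woman's home visit 1 score as covariate. Home visit 1 scores will be summarised by group for description only.

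An equivalent is one linear mixed model with arm, visit, arm-by-visit, the home visit 1 score and a random effect for woman, reporting the arm contrast at each follow-up visit.

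The cost is small. The score is already collected, SAS 9.4 fits either model, and no new data are needed. Each model spends one degree of freedom. A rule is needed for women without a home visit 1 score, either mean imputation of the covariate or exclusion from that model. The Data Availability section says the data had not been analysed at the time of writing, so the wording could be settled before analysis.

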**Methods/design:**

PREVED (Pregnancy, PreVention, Endocrine Disruptors) is an open-label randomized controlled trial assessing the impact of environmental health education intervention on EDC exposure during pregnancy. Inclusion, consent, and randomization take place during the first trimester. The participants are randomly allocated into three groups: (i) control group (information leaflet on EDCs), (ii) intervention group in neutral location (information leaflet and workshops in a meeting room), and (iii) intervention group in contextualized location (information leaflet and workshops in a real apartment). Workshops are organized between the second and third trimesters of pregnancy. Main outcome is the percentage of participants who reported consuming manufactured/industrial food. Secondary outcomes are as follows: (i) psycho-social dimensions, (ii) EDC concentrations in urine, (iii) EDC concentration in colostrum, and (iv) percentage of participants who reported consuming paraben-free personal care products.

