#### Secondary outcomes

Mean score of psychosocial questionnaire (Q2) developed by our team, whose dimensions are presented in Table 4Urinary concentrations of: BPA, chlorinated derivatives of BPA, methyl-, ethyl-, propyl-, and butyl-PBConcentration in colostrum of: BPA, methyl-, ethyl-, propyl-, and butyl-PBPercentage of participants who reported consuming PB-free personal care products

**Table 4 Tab4:** Dimensions of the psychosocial questionnaire used in PREVED study

Dimension of the psychosocial questionnaire	Origin of corresponding question or questions	Comment
***Self-esteem***	French version of the “Self-esteem scale” [49]	Score ranges from 10 to 40: the lower the score, the lower self-esteem. Items for this score are self-administered
***Perceived health***	Created for the questionnaire	Score ranges from 0 to 100 on a visual analogic scale
***Health care renunciation and risk aversion***	Inspired by French national investigations [50, 51]	Use of visual analogic scales
***Risk perception***	Created for the questionnaire and based on the Perception of Pregnancy Risk Questionnaire [52]	Use of visual analogic scales. A composite and global score of perinatal risk perception related to EDC exposure was created
***Knowledge about endocrine-disrupting chemicals (EDCs):*** routes and sources of exposure, ability to name some EDC’s molecules or families of molecules and definition of an EDC	Created for the questionnaire	A composite score was created. A catalog of photo images illustrates sources of exposure
***Perceived knowledge about EDCs***	Created for the questionnaire	Use of a visual analogic scale
***Expectations for a “healthy baby”***	Based on “the healthy baby concept” [53]	Use of a visual analogic scale and a catalog of photo images
***Trusted person***	Created for the questionnaire	The answer to this question aims to identify the trusted person, who exerts the most influence on the pregnant woman
***Level of concern about five risks related to pregnancy***	Created for the questionnaire	This exploration is meant to establish a hierarchy, with respect to chemical risk concerns. A catalog of photo images is used
***The way the pregnant woman heard about EDCs and, if so, how she experienced the information she received***	Created for the questionnaire	These two parameters explore the role of information provided by the media, professional studies, and relationships (personal, friendly, professional, health professionals)

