***Relationship to risk visibility***	Created for the questionnaire	Likert-type response

The planning of the administration of questionnaires and the collection of samples is summarized in Fig 2.

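### ANOVA is prescribed for every Q2 dimension, although at least part of two of the 11 dimensions is nominal and has no mean to compare

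*Protocol article*

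**What the plan says.** All of this is in the protocol article.

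- **Outcome definition (Secondary outcomes).** The first secondary outcome is "Mean score of psychosocial questionnaire (Q2) developed by our team", followed by a pointer to Table 4 for its dimensions.
- **Same outcome in the abstract (Methods/design).** "Secondary outcomes are as follows: (i) psycho-social dimensions", in the plural.
- **Group comparison (Data collection, management, and analysis).** "The results of Q2 in the three groups will be compared by dimension using ANOVA analyses". No dimension is exempted, and no other between-group test is named for Q2.
- **Response formats (Table 4).** Some rows are plainly numeric. For self-esteem the table says "Score ranges from 10 to 40: the lower the score, the lower self-esteem", and for perceived health "Score ranges from 0 to 100 on a visual analogic scale". Others are not described as scores. For the trusted person: "The answer to this question aims to identify the trusted person, who exerts the most influence on the pregnant woman". For the level of concern about five risks: "This exploration is meant to establish a hierarchy, with respect to chemical risk concerns". For the relationship to risk visibility: "Likert-type response".

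**The concern.** ANOVA compares group means, so it needs an answer whose mean says something. The name of the person a woman trusts most, or the channel through which she learned about endocrine disruptors, is a category without order. If such categories are given numeric codes, the group means and the F statistic depend on the arbitrary order of the codes. Two arms with quite different answers can then show the same mean: one arm where everybody falls in the middle code, and another split evenly between the two outer codes.

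At stake is the group comparison for these items. Followed literally, the plan gives an uninterpretable p-value for them. If the analyst sees the problem and switches method, the replacement is chosen at analysis, in an open-label trial, rather than stated beforehand. The primary outcome, the reported consumption of manufactured food, is not affected.

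**Working it through.** No sample size, power or alpha figure enters this point. The check is a count of the Table 4 rows and a classification of each by its stated format, set against the ANOVA sentence.

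| Table 4 dimension | Format given | Is there a mean to compare? |
|---|---|---|
| Self-esteem | score, 10 to 40 | yes |
| Perceived health | visual analogue scale, 0 to 100 | yes |
| Care renunciation and risk aversion | visual analogue scales | yes |
| Risk perception | visual analogue scales, composite | yes |
| Knowledge about endocrine disruptors | composite | yes |
| Perceived knowledge | visual analogue scale | yes |
| Expectations for a healthy baby | visual analogue scale plus photo catalogue | yes, for the scale |
| Trusted person | identity of a person | no |
| How she heard about endocrine disruptors, and how she experienced it | two parameters; the source is a category (media, professional studies, relationships), the format of the experience is not given | no, for the source |
| Level of concern about five risks | aims at a hierarchy; the row title speaks of a level | debatable |
| Relationship to risk visibility | Likert-type | debatable |

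Counts:

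- Total rows: 11.
- Rows with a score, scale or composite: 7.
- Rows not described as a score: 11 − 7 = 4, and 4/11 = 36%.
- Of those four, rows where ANOVA has no meaning for at least part of the row: 2, and 2/11 = 18%.
- Rows where ANOVA can be computed but is open to debate: 4 − 2 = 2.

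Next, does any other sentence of the analysis section supply the missing method?

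1. The descriptive analysis gives percentages for qualitative variables. That summarises the nominal items but does not compare arms.
2. The chi-square test is named for Q1 and the chemical concentrations, not for Q2.
3. Logistic regression is planned for factors influencing the main and secondary outcomes. It needs a categorical outcome, but no category or cut is stated for Q2, and it is not presented as the comparison of the three groups.

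So for the two nominal items the only stated comparison is ANOVA.

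Last, the outcome label. Read alone, a mean score of the questionnaire suggests one total. The same sentence points to the dimensions, the abstract and the secondary objectives speak of psychosocial dimensions, and the analysis runs dimension by dimension. Together these support one mean score per dimension. That reading works for the seven scored rows and leaves four rows without a stated score.

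**The case against.** The strongest reply is that this is a condensed article. Item scoring and item-level tests commonly sit in the full protocol or the analysis plan, and an analyst would hardly run ANOVA on the identity of a trusted person. The plan also does not treat everything as numeric, since it has percentages for qualitative variables and a logistic model. Part of this stands: missing scoring rules are no finding, and none is claimed. But the article does not stay silent. It names a test for all dimensions, and its own Table 4 shows that the test does not fit two of them.

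A reader might infer more, and the documents do not support it:

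- **That the outcome does not exist.** No section proposes pooling the 11 dimensions into one total. One mean score per dimension is the reading that agrees with the abstract and the analysis section, and seven rows have such a score.
- **That ANOVA cannot be run on all four rows without a stated score.** ANOVA on Likert codes is computable, and preferring an ordinal model is a matter of choice. For the five risks, the hierarchy is a stated purpose; the row title leaves room for a rating of each risk. In the row on how she heard about endocrine disruptors, only the source is clearly nominal.
- **That the many dimensions give a known, high false-positive rate.** With independent tests at 0.05, 11 tests would give 1 − 0.95^11 = 43%, and 22 tests (11 at each of two follow-up visits) 1 − 0.95^22 = 68%. These figures count ANOVAs on the nominal items, for which the test has no meaning, and the article does not state one test per visit. For the seven scored rows alone the figures would be 1 − 0.95^7 = 30% and 1 − 0.95^14 = 51%, and correlation between dimensions lowers all of them. A lead score and multiplicity control among secondary outcomes are commonly left to the analysis plan, so neither is part of this point.

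**Conclusion.** The point holds in a narrow form and is minor. The blanket ANOVA is wrong for at least part of two of the 11 dimensions (18%): the trusted person and the source of information. For two further dimensions it is computable but debatable, and for the remaining seven it can stand. The outcome label should be made to match the analysis by dimension; as worded it is ambiguous, not void.

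This rests on the formats in Table 4 being complete enough to classify the rows. If the full protocol turns the trusted person or the information source into a numeric score, the mismatch for that item would go away; nothing in the article suggests this. Only a secondary outcome is affected.

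**What to change.** 1. **Secondary outcomes:** define the Q2 outcome as the mean score of each scored dimension, so that it agrees with the abstract and the analysis section.
2. **Data collection, management, and analysis:** restrict ANOVA (or a linear model) to the seven dimensions with a score, visual analogue scale or composite.
3. **Same section:** compare the nominal answers (trusted person, source of information) between the three groups by a chi-square test or a multinomial model.
4. **Optional:** use an ordinal method for the concern about five risks and the Likert-type item, once their response format is stated.

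The cost is a few sentences. No data collection, sample size or primary analysis changes, and the Data Availability section says that the data had not yet been analysed. One practical limit: the article does not list the answer categories. If some are rare, the rule for merging them should be written down before the answers are tabulated by arm.
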